#### Eligibility criteria

Asian patients aged 2 to 17 years on obtaining informed consent.Those definitively diagnosed with CD30-positive HL or sALCL based on histological findings. A report or its copy describing that a specimen collected at the time of initial diagnosis or relapse was evaluated as positive for CD30 using an immunohistochemical procedure or flow cytometry is stored in the hospital.Those with PD during standard chemotherapy or without CR/partial remission (PR) after treatment, or those with relapse or additional exacerbation after standard chemotherapy.Those with an Eastern Cooperative Oncology Group performance status (PS) of 0 to 2.Those whose laboratory data on screening meet the following criteria. The administration of a gene recombinant human granulocyte-colony stimulating factor (G-CSF) preparation or blood transfusion is not performed within1 week before neutrophil and platelet count tests:
Neutrophil count: ≥1500 × 10^6^/LPlatelet count: ≥75,000 × 10^6^/LHemoglobin level: ≥8 g/dLSerum bilirubin level: ≤1.5-fold the upper limit of normal (ULN) in the facilitySerum creatinine level: ≤1.5-fold the ULNAlanine aminotransferase (ALT) and aspartate aminotransferase (AST): ≤2.5-fold the ULN
6)Those who are expected to survive for ≥3 months on obtaining informed consent.7)Written informed consent regarding participation in this clinical study could be obtained from subjects and/or representatives

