**Methods:**

Phase I clinical study of SGN-35 involving children with recurrent or refractory CD30-positive Hodgkin’s lymphoma or systemic anaplastic large cell lymphoma (BV-HLALCL study) is being conducted for pediatric patients in order to evaluate the safety, feasibility and preliminary clinical effectiveness of brentuximab vedotin. SGN-35 is intravenously administered on Day 1 of each cycle (21 days/cycle). The dose of SGN-35 is calculated based on the body weight at the baseline. The primary endpoint is dose limiting toxicity and incidence of adverse events. The secondary endpoints are pharmacokinetics, response rate, complete remission rate, response duration, progression-free survival and event-free survival. The reduction rate of tumor will be calculated according to revised response criteria for malignant lymphoma for measurable tumor. Six pediatric patients will be enrolled in this study.

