#### Study setting and protocol review

This is a single-arm, open-label, multicenter phase I study involving four institutions: Hokkaido University Hospital, St. Marianna University School of Medicine Hospital, National Hospital Organization Nagoya Medical Center, and Kyushu University Hospital. The protocol has been reviewed and approved by institutional review boards of each institutions.

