7)Those with intra-cerebral or meningeal infiltration.8)Those with signs or symptoms suggesting progressive multifocal leukoencephalopathy.9)Those with a history of severe hypersensitivity or allergy.10)Human immunodeficiency virus antibody-, hepatitis B virus surface antigen (HBs) -, hepatitis B virus surface antigen antibody-, hepatitis B virus core antigen antibody-, or hepatitis C virus antibody-positive patients on a screening test. However, patients with a history of hepatitis B vaccination who are positive for HBs antibody alone will not be excluded.11)Patients with liver cirrhosis.12)Those in whom autologous stem cell transplantation was performed within 12 weeks before the initial administration of SGN-35.13)Those in whom allogeneic stem cell transplantation was performed.14)Those who received treatment for malignant tumors (radiotherapy, chemotherapy, and hormonal therapy) within 2 weeks before the initial administration of SGN-35. However, those who received biological preparations in a longer period: either 6 weeks before the initial administration of this drug or a period corresponding to 5-fold the half-life, will be excluded.15)Those who received the systemic administration of adrenocorticohormones at a non-steady dose within 1 week before the initial administration of SGN-35.16)Those who took drugs that inhibit CYP3A4 (clarithromycin, itraconazole, verapamil, and diltiazem) or ingested foods/supplements (such as grapefruit) within 1 week before the initial administration of SGN-35.17)Those who took drugs that induce CYP3A4 (phenytoin, phenobarbital, rifampicin, carbamazepine) or ingested foods/supplements (such as St. John’s wort) within 2 weeks before the initial administration of SGN-35.18)Those to whom other investigational drugs were administered within 4 weeks before the initial administration of SGN-35.19)Those in whom medical instruments under a clinical study were used within 4 weeks before the initial administration of SGN-35.20)Those with hypersensitivity to additives contained in the composition of SGN-35.21)Pregnant (human chorionic gonadotropin-positive) or lactating patients.22)Those who are not willing to conduct appropriate contraception from informed consent acquisition until 6 months after the final administration of the investigational drug.23)Those with positive reactions on a pregnancy test at the time of screening.24)Those in whom the chief investigator/investigators considered it difficult to perform this clinical study.

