### Dose-limiting toxicity (DLT)

DLT should be evaluated from the initial administration of this drug until administration on the first day of administration in Cycle 2. In subjects in whom the appearance of toxicity made this-drug administration in Cycle 2 impossible, and treatment was discontinued, DLT must be evaluated until safety follow-up.

Among adverse events of which the association with this drug cannot be ruled out, those corresponding to the following items are regarded as DLT. The grade is evaluated according to “Common Terminology Criteria for Adverse Events v4.03”:Grade 4 neutropenia persisting for ≥8 daysGrade 3 febrile neutropenia requiring the administration of antibioticsGrade 4 febrile neutropeniaGrade 4 thrombocytopenia

Grade 3 ≤ non-hematological toxicity. However, the followings are excluded:Grade 3 fatigueGrade 3 or 4 nausea (supportive therapy is permissible)Grade 3 or 4 vomiting (supportive therapy is permissible)Grade 3 abnormalities in non-hematological laboratory data showing recovery to grade 1 or a baseline condition (cases in which there were abnormalities at study enrollment) within 14 daysGrade 3 or 4 allergic reactions

DLT will be finally evaluated by the trial-coordinating investigator.

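### Entry at every age from 2 to 17 turns on ECOG performance status, a scale whose work and self-care grades have no clear meaning in young children

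*Protocol article*

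**What the plan says.** The Eligibility criteria open with age: "Asian patients aged 2 to 17 years on obtaining informed consent". A few items later comes the only performance requirement: "Those with an Eastern Cooperative Oncology Group performance status (PS) of 0 to 2". It carries no age qualifier, and neither this list, the Exclusion criteria nor any other section names a second scale or a convention for scoring small children.

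Other entry criteria also bear on general condition. The Eligibility criteria require an expected survival of at least 3 months. The last exclusion gives general discretion: "Those in whom the chief investigator/investigators considered it difficult to perform this clinical study".

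The study is small and multicentre. The abstract states: "Six pediatric patients will be enrolled in this study". Study setting and protocol review states: "This is a single-arm, open-label, multicenter phase I study involving four institutions". Under Treatment methods, three further children may be added if 2 of the first 6 have a dose-limiting toxicity (DLT).

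**The concern.** A performance criterion should separate children who are fit enough for the study from those who are not, and do so in the same way for each child. ECOG was built around adult activity: its grades describe ability to work and to look after oneself. A healthy 2-year-old does neither independently. Read literally, the grades say little about whether such a child is well. Read loosely, they depend on how the assessor translates them.

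The cut-off lies between grades 2 and 3, so any doubt in the translation becomes doubt about eligibility. A young child could be refused because of normal dependence on carers, or admitted on a generous reading. Safety and tolerance are the primary objective, and tolerability is judged on very few children, so it matters that the entry rule means the same for each of them.

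**Working it through.** The article has no figure to reproduce: the number of children is not derived from a power calculation, and no calculation depends on performance status. The check is a comparison of the text.

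1. **Age range.** Whole years 2 to 17 give 17 − 2 + 1 = 16 single-year ages, all eligible (Eligibility criteria).
2. **Scale.** One scale, ECOG, with one cut-off (0 to 2 in, 3 or worse out) applies to all 16 (same list).
3. **Fit of the scale.** The article does not reproduce the grade definitions. That they rest on work and self-care is general knowledge of the scale, and it is the one outside premise here. Given that premise, the definitions can be applied much as written to a 17-year-old, but at age 2 they cannot be applied without an interpretive rule.
4. **Interpretive rule.** None is stated. This is not a detail that the article leaves out: the scale and its cut-off are both given, and as given they do not suit the lower part of the stated age range.
5. **Other criteria that might take its place.** Expected survival and investigator discretion (see above) also screen for general condition. Both are judgements without a graded scale, so neither says how to separate grade 2 from grade 3 in a small child.
6. **Reach of a split at 16.** Taking under 16 as an example, an alternative scale would cover ages 2 to 15, which is 14 of the 16 single-year ages, and ECOG would remain for ages 16 and 17. This counts ages, not expected patients; the article gives no age distribution.

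**The case against.** The strongest reply is that this is a condensed article. The full protocol may tell sites how to score young children, and experienced paediatric investigators may manage without instruction. The article does not show that any child would be wrongly scored or that the four sites would differ, and the number of toddlers expected is unknown. All of that stands, and it limits the point to a possible inconsistency. It does not remove the point, because the article states a single scale for every age, and that statement does not suit the younger children.

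A reader might go further in four ways that the document does not support.

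- **Renal impairment at entry.** Creatinine, bilirubin and the transaminases are limited by multiples of the upper limit of normal (ULN), for example "≤2.5-fold the ULN" for the transaminases, without mention of age. It is tempting to infer that an adult creatinine limit would admit a small child with poor renal function. The article never says that the limits are adult or independent of age. The reference to the facility stands with bilirubin and reaches creatinine only through the shared abbreviation, and a facility's limits may already be age-specific. Any estimate of renal function at the limit would need a ULN, a height and a formula, none of which is in the article. The definition may also be left to the full protocol.
- **DLT grading.** One might think that laboratory DLTs are judged against the same limits. The Dose-limiting toxicity section cites CTCAE v4.03, and its wording on "recovery to grade 1 or a baseline condition" mentions no ULN and no entry limit.
- **Sole safeguard.** ECOG is not the only check on general condition, as the survival and discretion criteria show.
- **Weight of one child.** One child in six is 1/6, about 17%. That is one child's share of the first cohort and says nothing about how likely a misclassification is.

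**Conclusion.** The point holds for performance status. Requiring ECOG 0 to 2 from age 2 upward applies a scale to children for whom its grades have no clear literal meaning, so decisions at the 2/3 boundary could be inconsistent. The conclusion rests on what the article states and on the general character of ECOG, and it assumes that no scoring convention in the full protocol already deals with young children.

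Its size cannot be given as a number. It depends on how many young children are enrolled and how many of them lie near the boundary, and the article reports neither. The number of children and the DLT rule are unaffected. The age basis of the laboratory ULNs is at most a clarification request, and the article supports no conclusion about renal impairment.

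**What to change.** In the Eligibility criteria, replace ECOG for younger children, for example those under 16, with an age-appropriate scale such as Lansky play-performance, and keep ECOG for the oldest patients. The sponsor should set and state the cut-off that corresponds to ECOG 0 to 2, and the age at which the scale changes. If the full protocol already has a convention for young children, cite it in the criterion.

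The cost is a short change to one criterion and one extra item on the case report form, with performance status then reported on two scales at baseline. No new test is needed.

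As a separate and lesser request, the sponsor could confirm whether the laboratory ULNs are age-specific at each site.

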#### Exclusion criteria

Patients diagnosed with primary ALCL of the skin as the latest diagnosis (those with infiltration in other organs and a sALCL-like condition are regarded as eligible).Those after the resection of all lesions.Those with active viral, bacterial, or fungal infection within 2 weeks before the initial administration of SGN-35.Those with ≥grade III heart failure (New York Heart Association (NYHA) severity classification), refractory coronary disease, arrhythmia, a left ventricular ejection fraction of < 50%, angina pectoris, or acute ischemia or active conduction disorder on electrocardiography, or those with a history of myocardial infarction within 6 months before the initial administration of SGN-35.Those with refractory diabetes.Those with a history of other malignant tumors persisting for ≥3 years and complications. However, the following cancers are excluded:
Completely resected non-melanoma skin cancerCompletely resected intraepithelial carcinoma
7)Those with intra-cerebral or meningeal infiltration.8)Those with signs or symptoms suggesting progressive multifocal leukoencephalopathy.9)Those with a history of severe hypersensitivity or allergy.10)Human immunodeficiency virus antibody-, hepatitis B virus surface antigen (HBs) -, hepatitis B virus surface antigen antibody-, hepatitis B virus core antigen antibody-, or hepatitis C virus antibody-positive patients on a screening test. However, patients with a history of hepatitis B vaccination who are positive for HBs antibody alone will not be excluded.11)Patients with liver cirrhosis.12)Those in whom autologous stem cell transplantation was performed within 12 weeks before the initial administration of SGN-35.13)Those in whom allogeneic stem cell transplantation was performed.14)Those who received treatment for malignant tumors (radiotherapy, chemotherapy, and hormonal therapy) within 2 weeks before the initial administration of SGN-35. However, those who received biological preparations in a longer period: either 6 weeks before the initial administration of this drug or a period corresponding to 5-fold the half-life, will be excluded.15)Those who received the systemic administration of adrenocorticohormones at a non-steady dose within 1 week before the initial administration of SGN-35.16)Those who took drugs that inhibit CYP3A4 (clarithromycin, itraconazole, verapamil, and diltiazem) or ingested foods/supplements (such as grapefruit) within 1 week before the initial administration of SGN-35.17)Those who took drugs that induce CYP3A4 (phenytoin, phenobarbital, rifampicin, carbamazepine) or ingested foods/supplements (such as St. John’s wort) within 2 weeks before the initial administration of SGN-35.18)Those to whom other investigational drugs were administered within 4 weeks before the initial administration of SGN-35.19)Those in whom medical instruments under a clinical study were used within 4 weeks before the initial administration of SGN-35.20)Those with hypersensitivity to additives contained in the composition of SGN-35.21)Pregnant (human chorionic gonadotropin-positive) or lactating patients.22)Those who are not willing to conduct appropriate contraception from informed consent acquisition until 6 months after the final administration of the investigational drug.23)Those with positive reactions on a pregnancy test at the time of screening.24)Those in whom the chief investigator/investigators considered it difficult to perform this clinical study.

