Events include death, progression of disease, secondary cancer, and toxicity-related discontinuation. Toxicity-related discontinuation refers to the discontinuation of this clinical study related to adverse events of which the relationship with this drug cannot be ruled out. EFS refers to the interval from the first day of administration until the earliest day of event appearance. If there are no events, the subject is censored at the final day of observation. If it is discontinued due to transplantation or withdrawal in the absence of events, they are censored at the day of study discontinuation. If subjects receive new anti-tumor treatment other than stem cell transplantation, they are censored at the start of the treatment.

The anti-tumor effects of SGN-35 are evaluated only in patients with measurable lesions according to the Revised Response Criteria for Malignant Lymphoma [13].

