### Efficacy assessment method

The anti-tumor effects of SGN-35 are evaluated only in patients with measurable lesions according to the Revised Response Criteria for Malignant Lymphoma [13] based on the results of cervical, thoracic, abdominal, and pelvic computed tomography (CT) and positron emission tomography (PET), which were performed at the points established in the study protocol. At each point, the treatment response is assessed as CR, PR, SD, or PD. Lesions meeting the following criteria are regarded as measurable:Nodular masses of lymph nodes or extranodular organs evaluated as lymphoma on CTThe lesion can be clearly measured in two intersecting directions on cross sections of CT.The maximum diameter exceeds 1.5 cm on cross sections of CT.Positive findings on FDG-PET.

Among measurable lesions, 6 lesions at maximum in the order of maximum diameter on cross sections of CT should be selected as target lesions regardless of nodular or extranodular lesions.

If subjects are positive for bone marrow infiltration on baseline assessment, follow-up by bone marrow aspiration or biopsy may be necessary. To evaluate the treatment response as CR, subjects must be negative for bone marrow infiltration. If morphological examination-based evaluation is impossible, the results of examination using immunostaining should also be considered.

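### As printed, the other-malignancy exclusion does not exclude a child whose other cancer is of less than 3 years' standing, and leaves unclear whether a concurrent cancer is excluded

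*Protocol article*

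**What the plan says.** The sixth item of the Exclusion criteria in the protocol article rules out "Those with a history of other malignant tumors persisting for ≥3 years and complications". It continues "However, the following cancers are excluded" and lists completely resected non-melanoma skin cancer and completely resected intraepithelial carcinoma. In context, the word excluded there must mean exempt from the exclusion.

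Four other places bear on the point:

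- Eligibility criteria, age: "Asian patients aged 2 to 17 years on obtaining informed consent".
- End points, EFS: "Events include death, progression of disease, secondary cancer, and toxicity-related discontinuation". Time runs from the first day of administration to the earliest event.
- Efficacy assessment method: a measurable lesion must be a mass judged to be lymphoma on CT, be clearly measurable in two directions, exceed 1.5 cm and show "Positive findings on FDG-PET".
- Safety endpoints: adverse event incidence is calculated in the safety analysis set, which is everyone enrolled who received at least one administration.

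**The concern.** An exclusion for other malignancies normally serves to keep out patients whose second cancer is active or recent enough to affect the results. Here the 3-year figure is a minimum duration. A child whose other cancer was found 6 months or 2 years ago does not meet it. If the words after the 3-year figure add a second condition, the exclusion is narrower still.

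In a single-arm study of six children there is no comparator to absorb such a case. A recurrence of, or death from, an earlier cancer could be counted as an EFS event, and its symptoms could enter the adverse event table, although neither reflects the drug or the lymphoma. Four institutions apply the item, and they could read it differently. The reading also affects who is analysed, because the full analysis set drops patients found ineligible after enrolment.

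**Working it through.** The protocol article states no figure on this point, so there is nothing to reproduce. The check is mainly a comparison of wording, with simple arithmetic for scale.

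**1. Who meets the item, on each reading**

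| Child's other malignancy | *Complications* = a further condition | *Complications* = a coexisting cancer |
|---|---|---|
| Past, under 3 years' standing | not excluded | not excluded |
| Concurrent, under 3 years' standing | not excluded | excluded, if the *and* is taken to join two separate grounds |
| 3 years' standing or more | excluded only with complications | excluded |

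The first row is the same in both columns, so the gap for recent cancers does not depend on the reading. The second row does. A child between the second and third birthday cannot meet a 3-year duration at all, although entry starts at age 2.

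**2. Direction of the window**

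The other time-limited exclusions all remove recent events: infection within 2 weeks, myocardial infarction within 6 months, autologous transplantation within 12 weeks, anti-cancer treatment within 2 weeks, investigational drugs within 4 weeks. This item alone removes the long-standing. Its exceptions are for fully resected tumours, and it makes little sense to exempt those while admitting recent, unresected ones.

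**3. Other criteria that might close the gap**

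- Exclusion 14: "Those who received treatment for malignant tumors (radiotherapy, chemotherapy, and hormonal therapy) within 2 weeks before the initial administration of SGN-35", with a longer window for biological preparations. A child off treatment for longer passes.
- Exclusion 24: "Those in whom the chief investigator/investigators considered it difficult to perform this clinical study". This is discretion, not a rule.
- Eligibility criteria: "Those who are expected to survive for ≥3 months on obtaining informed consent", and performance status 0 to 2. A child with a recent second cancer can satisfy both.

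Each is a partial backstop. None excludes a second cancer as such.

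**4. Endpoint by endpoint**

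- EFS: death counts whatever its cause, and secondary cancer is not limited to a cancer that arises after the first dose. Directly exposed.
- Adverse events: incidence is tabulated in all treated children, for adverse events as well as reactions to the drug, so attribution to the drug is not needed to be counted. Exposed.
- Response: lesions must be judged to be lymphoma. Weakly exposed.
- DLT: only events whose association with the drug cannot be ruled out count, and the trial-coordinating investigator makes the final evaluation. Weakly exposed.

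**5. Scale**

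Inputs: 6 children in Cohort 1 and 3 more in Cohort 2 (Treatment methods).

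- One child's share of an incidence: 1/6 = 16.7%; 1/(6 + 3) = 1/9 = 11.1%.
- Exact (Clopper-Pearson) 95% intervals at n = 6: 0/6 gives 0 to 45.9%; 1/6 gives 0.4 to 64.1%.
- Kaplan-Meier EFS: one event with k children at risk multiplies the estimate by 1 − 1/k. With all six at risk it falls from 1 to 5/6 = 83.3%.

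**6. A bound for DLT, not an expected effect**

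Let p be the true DLT rate, and assume Cohort 2 always opens after 2 of 6. Then P(tolerable) = P(at most 1 of 6) + P(2 of 6) × P(0 of 3). At p = 0.20 this is 0.655 + 0.246 × 0.512 = 0.781. If one of the six is certain to be counted as a DLT because of a second cancer, it becomes P(0 of 5) + P(1 of 5) × P(0 of 3) = 0.328 + 0.410 × 0.512 = 0.537. The same calculation gives 0.957 to 0.830 at p = 0.10 and 0.531 to 0.292 at p = 0.30.

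**The case against.** The strongest reply is that this is loose translation in a condensed article, not a design decision. The same item uses the word excluded to mean exempt, so its English is unreliable. The full protocol may state the window correctly, and sites would work from that. This stands as far as it goes: the article cannot show what was intended or how sites apply the item. It does not make the printed sentence right, and an eligibility rule is not something a statistical analysis plan would repair.

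Three stronger readings are tempting, and the document does not support them.

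- *A concurrent cancer is admitted.* This follows only if *complications* is a further condition. If it means a coexisting cancer, concurrent malignancy is already excluded. The text does not settle this.
- *A second tumour would corrupt the response rate.* PET positivity alone does not make a lesion measurable. The mass must also be judged to be lymphoma, so a second tumour would have to be misclassified first.
- *The tolerability verdict is at risk to the extent of the bound in step 6.* That bound assumes both that such a child enters and that the event is counted as a DLT. The causality condition and the final evaluation of DLT work against the second, so the drop from 0.781 to 0.537 is not the size of this problem.

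It can also be said that a cancer known at entry does not newly appear during follow-up, and so is not a secondary cancer event. That is a reasonable reading of the EFS definition, but it is not stated, and it does not cover recurrence of a recent cancer or death from it. Finally, 1 of 6 is the weight of any child in this trial. That is true: the figure shows how little room there is for error, not how likely the error is.

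**Conclusion.** The criterion is wrong as written, at low severity. On either reading of its last words, a child with a recent other malignancy is not excluded by this item, contrary to the direction implied by its own exceptions, and no other criterion excludes such a child categorically. The status of concurrent malignancy is ambiguous.

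The consequence is confined mainly to EFS and adverse event incidence. If one such child entered and had a relevant event, that event would move an incidence by about 17 percentage points at six children or 11 at nine. It would not make the response or safety results as a whole unattributable to the drug.

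The low severity rests on an assumption that the document does not quantify: that second cancers in 2- to 17-year-olds with these lymphomas are rare. The view that recent cancers were the intended target is an inference from the exceptions and the neighbouring items, and needs confirmation from the full protocol.

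**What to change.** Check the sixth exclusion item against the full protocol and reword it as follows:

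1. Make the time window run in the intended direction, so that recent and not only long-standing other malignancies are excluded. The 3-year length is the document's own figure and should be confirmed at the same time.
2. Replace the reference to complications with an explicit statement of whether a concurrent other malignancy is excluded.
3. Keep the two resected-tumour exceptions, worded as exempt from the exclusion.
4. In the EFS definition, specify that secondary cancer means a new cancer arising after the first dose, and say how recurrence of a cancer that predates entry is handled.

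The cost is one sentence in the Exclusion criteria and one clause in the End points section. The effect on accrual should be negligible on the same rarity assumption. If the full protocol already has the correct wording, only the article needs correcting. If it does not, the eligibility text needs amending, and the children already enrolled should be checked against the corrected item.
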